#### **5.1.4 Withdrawal of Patients**

Patients may be withdrawn from further participation in the study for any the following reasons:

- At their own request without giving reasons (including drop-outs and patients lost to follow-up).
- At the discretion of the investigator, at any time during the study period also in case the investigator considers the patient is not treated appropriately during the course of the study.
- Development of AE, laboratory abnormality, inter-current illness, or other medical condition or situation such that continued participation in the study would not be in the best interest of the patient.
- Meeting any exclusion criteria (either newly developed or not previously recognized).

IMP administration should be interrupted in case of worsening of the health status; medical conditions to be taken into consideration may include but not be limited to pain, gastrointestinal disorder, skin reactions, bleeding of the skin, excretion of blood from intestine or urinary tract or profuse bruises.

If a patient is prematurely withdrawn, a complete final examination as detailed in Section 4.2 is to be performed at the time of withdrawal and the reason for withdrawal has to be documented.

Withdrawn patients will not be replaced.

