## 2.4 Potential Risks and Benefits

### 2.4.1 Potential Risks

Due to its mode of action, bleeding may occur during ancrod treatment. The direct effect of ancrod on the coagulation cascade and on platelet function may cause microscopic hematuria, bleeding at puncture sites, bruising and, in rare cases, melena, epistaxis, and hematemesis (Latallo, 1983). Many bleeding adverse events are related to bruising and are of limited clinical significance. The

|                                |                             |                      |
|--------------------------------|-----------------------------|----------------------|
| Protocol Amendment 7.1         | Study no.: NM-V-101         | Page 23 of 85 |
| Date of Amendment: 15 Feb 2018 | EudraCT No.: 2012-000066-37 |                      |

bleeding risk appears to be increased when fibrinogen levels remained below 40 mg/dL for longer periods.

The relatively high incidence of adverse events observed in clinical studies in patients with acute ischemic stroke treated with ancrod may be attributed to advanced age, predisposition, and vulnerability of this patient population and cannot be extrapolated to patients with sudden hearing loss who will be treated with a different, moderate dosing regimen. Further, the incidence of adverse events observed in the direct comparison of defibrinogenation therapy with corticosteroid revealed no minor or major bleeding. Side effects were observed in 84.9% of patients who received defibrinogenation therapy and in 85.9% of patients who received corticosteroid treatment (Kubo et al., 1988).

Local reactions, such as urticaria and exanthema, are rare but may occur after subcutaneous use. Some patients who had received ancrod subcutaneously developed local irritation or itching. These skin reactions have responded to antihistamine therapy. There was no evidence of an allergic reaction in healthy subjects or in patients treated with ancrod repeatedly. Nevertheless, special attention should be paid to patients receiving a second course of ancrod because neutralizing antibodies may occur particularly after long-term subcutaneous administration.

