99 patients are planned to be enrolled, 66 patients on ancrod and 33 on placebo. The recruitment period will be approximately 57 months. The study duration for each patient will be 90 days.

Screening measurements (for details see Section 4.1) prior to initiation of study drug administration on Day 1 (Visit 1) will include an assessment of plasma fibrinogen concentration in the local laboratory. Immediately after randomization on Day 1 (Visit 1), patients will receive the initial infusion of investigational product. The initial dose of ancrod will be adjusted according to the screening fibrinogen concentration by using different infusion durations at a constant infusion rate (see Section 7.1).

On the following day (Day 2, Visit 2), a venous blood sample will be taken for coagulation assays (fibrinogen, thrombin time [TT], prothrombin time [PT], activated partial thromboplastin time [aPTT]) to be performed in the selected responsible laboratory (local or central) of the site within 36 hours. The investigator must announce the taking of the blood sample for fibrinogen per fax to Nordmark (Pharmaceutical Development, unblinded personnel). Thereafter, on Day 2, a weight-adjusted ancrod dose of 1 IU/kg will be administered subcutaneously. Nordmark Pharmaceutical Development has to be informed immediately in writing (fax) from the responsible laboratory or designee on the result of the coagulation assays. The result of the coagulation assay may in principle not be communicated from the laboratory to the investigator or any other blinded study personnel. If the fibrinogen concentration on Day 2 is lower than 50 mg/dl the investigator will be informed by Nordmark Pharmaceutical Development that this patient may not receive further injections of ancrod on Day 4 and Day 6. This deviation has to be documented in the dosing worksheet. All other study related activities will be performed as planned. If the fibrinogen concentration on Day 2 is  $\geq 50$  mg/dl Nordmark Pharmaceutical Development will inform the investigator that the patient may receive further subcutaneous injections of 1 IU/kg ancrod on Day 4 and Day 6 (Visits 3 and 4) (Figure 1). Regardless of the result, Nordmark Pharmaceutical Development may not communicate any values to the investigator or any other blinded study personnel.

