### 5.1.3 Exclusion Criteria

The presence of any of the following will exclude a patient from study enrolment:

1. Pregnant or breast-feeding female.
2. positive pregnancy test before receiving study drug
3. Body weight > 140 kg
4. Bilateral SSHL.
5. Incomplete recovery after previous SSHL, when symmetric hearing was not reached again, according to patient's recollection.
6. Due to history of physical efforts suspected perilymph fistula or membrane rupture.
7. Previously existing, known retrocochlear hearing loss.
8. Any history of any ear operation or local inflammatory disease in the past one year.
9. History of blunt or penetrating ear trauma, head trauma, barotrauma, or acoustic trauma immediately preceding SSHL.
10. History of Menière's disease, autoimmune hearing loss, radiation-induced hearing loss, endolymphatic hydrops.
11. Any pre-treatment within the preceding 30 days prior to screening, ongoing treatment or planned treatment of SSHL-related hearing loss.
12. History of chronic inflammatory diseases or autoimmune diseases e.g. rheumatic disease, including rheumatoid arthritis, scleroderma, lupus erythematosus, polymyalgia rheumatica, polyarteritis nodosa, temporal/giant cell arteritis, Sjögren's syndrome, or ulcerative colitis and Crohn's disease.
13. History of unstable angina, coronary artery stenting or bypass grafting within three months of enrolment, transient ischemic attacks or stroke within four weeks of enrolment.
14. Prior chemotherapy or treatment with immunosuppressant drugs (azathioprine, chlorambucil, cyclophosphamide, or other alkylating agents), cyclosporine, etanercept, infliximab, interferon or any therapy with drugs known as ototoxic (e.g. aminoglycosides, cisplatin, loop diuretics, quinine etc.) in the past 6 months.
15. Gastrointestinal pathology: lesions liable to bleed such as active peptic ulcer disease, inflammatory bowel disease, history of gastrointestinal bleeding, or recent hemorrhage at any anatomical site requiring medical intervention.
16. Screening plasma fibrinogen level of <180 mg/dL.

|                                |                             |                      |
|--------------------------------|-----------------------------|----------------------|
| Protocol Amendment 7.1         | Study no.: NM-V-101         | Page 33 of 85 |
| Date of Amendment: 15 Feb 2018 | EudraCT No.: 2012-000066-37 |                      |

17. Known disorder of platelet function or coagulation abnormality.

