18. Platelet count of  $<100,000/\text{mm}^3$ .
19. Severe liver disease.
20. Hepatic failure (e.g., aspartate aminotransferase (SGOT) or alanine aminotransferase (SGPT)  $\geq 3 \times$  upper limit of normal [ULN]).
21. Treatment with hyperbaric oxygen within one week prior to study drug.
22. Renal insufficiency (e.g., blood urea nitrogen or creatinine  $\geq 2 \times$  ULN) or patients on renal dialysis.
23. Use of another investigational drug within 30 days prior to SSL onset.
24. Any other serious medical condition that might interfere with subject evaluation over the 90-day study period, based on the investigator's judgment, e.g. planned surgical intervention or any other condition which might give doubt for non-completing the study e.g. planned holiday, distance between investigational center and place of origin.
25. Known hypersensitivity to the drug substance or excipients
26. Blood or blood product infusion within one week prior to study drug.
27. Use of any prohibited drug listed in chapter 6.4.1 and 6.4.2 of this study protocol
28. Immunoglobulin infusion 4 weeks prior to study drug
29. Planned treatment using intramuscular injections (e.g. vaccinations, vitamin B therapy)
30. Conditions associated with an increased risk of hemorrhaging such as major surgery, history of hemorrhagic stroke, intracranial hematoma, subarachnoid hemorrhage, diabetic retinopathy, retinopathy grade 3 or worse, known hemostatic disorders.
31. Uremia and renal colic with calculus, cerebrovascular accident, and history of neurosurgery
32. History of malignant hypertension and/or diastolic pressure  $> 105 \text{ mmHg}$
33. Acute pericarditis
34. Subacute bacterial endocarditis
35. Septicemic states with or without evidence of diffuse intravascular coagulation
36. History of clinically relevant immediate-type allergy (type I) with respect to e.g. mildew, (house dust) mite, cockroach, hymenoptera venom, dog, cow and honeydew melon
37. Hearing loss of infectious or oncology origin

|                                |                             |                      |
|--------------------------------|-----------------------------|----------------------|
| Protocol Amendment 7.1         | Study no.: NM-V-101         | Page 34 of 85 |
| Date of Amendment: 15 Feb 2018 | EudraCT No.: 2012-000066-37 |                      |

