## 4. Data Analysis Considerations

### 4.1. Analysis Populations

All patients having signed informed consent and provide any data in the CRF, whether receiving study treatment or not, will be considered for analysis ("*Enrolled patients*"). All patients who have been given a patient number for randomization at Visit 1 are included in the *Randomized set* independently of having received IMP. The following analysis populations that will be used for statistical evaluation will be defined:

- **Safety Set (SFS):** It includes all patients who take at least one IMP dose and for whom any safety-related data or information after the first dose of IMP are available.  
Patients will be analyzed as treated. Analysis of safety variables will be based on the SFS.
- **Full Analysis Set (FAS):** It includes all patients being randomized and receiving at least one IMP dose, regardless of any protocol deviations.  
The intention-to-treat principle is preserved despite the exclusion of patients who took no IMP, as the decision of whether or not to begin treatment could not be influenced by knowledge of the assigned treatment.  
Patients will be analyzed as randomized. The FAS is the primary population and will be used to analyze all baseline/background and efficacy variables.
- **Per Protocol Set (PPS):** It includes only patients who receive at least one IMP dose and fulfil the following evaluability criteria: have SSHL as defined per inclusion criterion 1, provide valid PTA data for Visit 1 and Visit 5, and adhere reasonably well to the study protocol without major protocol deviations (see Section 4.5).  
The PPS is a subset of the FAS and represents the secondary analysis set for baseline/background and efficacy variables.

A definite allocation of patients to analysis sets is made at the BDRM (see Section 4.5).

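### Withdrawal from the study for newly meeting an exclusion criterion may lose Day 8 and later outcomes in a treatment-related way, and it conflicts with the rescue provisions

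*Combined protocol and SAP*

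**What the plan says.** Protocol 5.1.4 opens with "Patients may be withdrawn from further participation in the study for any the following reasons", and one listed reason is "Meeting any exclusion criteria (either newly developed or not previously recognized". Protocol 9.3 repeats the opening line and the bullet. Both sections also contain a separate paragraph on interrupting study drug when health worsens, with bleeding among the examples. Both require a complete final examination at withdrawal. Sections 5.1.4 and 4.5 refer that examination to 4.2, where the Day 8 list includes pure tone audiometry. After early termination, 4.5 asks only for a Day 30 antibody sample, if possible.

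Three entries in Protocol 5.1.3 matter here:

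- Criterion 15 includes "recent hemorrhage at any anatomical site requiring medical intervention". Section 2.4.1 says "Due to its mode of action, bleeding may occur during ancrod treatment".
- Criterion 11 includes "ongoing treatment or planned treatment of SSHL-related hearing loss".
- Criterion 27 is "Use of any prohibited drug listed in chapter 6.4.1 and 6.4.2 of this study protocol". The 6.4.1 list includes systemic corticosteroids.

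For a Day 2 fibrinogen below 50 mg/dl, sections 3.1 and 4.2 stop further injections but add "All other study related activities will be performed as planned".

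SAP 4.1 puts every randomized and dosed patient in the full analysis set (FAS) "regardless of any protocol deviations". SAP 5.3 keeps dropouts in that set, replaces a missing Visit 5 value by baseline, and leaves Visits 6 and 7 unimputed.

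**The concern.** Exclusion criteria are written to screen patients before randomization. Used afterwards as reasons to leave the study, some of them become events that treatment or outcome can bring about. A bleed that needs intervention is more likely on ancrod. Hearing-loss treatment started after Day 8 marks a patient who has not improved. Ineligibility recognized late is not caused by treatment, but the rule still allows measurement to stop in a patient whom the FAS must analyze.

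At stake are the Day 8 primary comparison, where a withdrawn patient may be entered as zero change, and the Day 30 and Day 90 comparisons, where the patient drops out of the data. SAP 2 expects only a few more evaluable patients than the 30 planned for the interim analysis, so one or two such patients can be visible in the result.

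**Working it through.** **1. The plan's own figure.** Protocol 10.1 assumes a 15 dB difference, SD 20 dB, two-sided 5%, 90% power and 2:1 allocation.

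Placebo n = (1 + 1/2) × (1.960 + 1.282)² × 20² / 15² = 1.5 × 10.51 × 1.778 = 28.02, rounded up to 29. With 58 on ancrod the total is 87, as stated (power 0.903 by noncentral t). With the 12% dropout rate of SAP 5.3, 87 / 0.88 = 98.9, so 99. Both figures reproduce. The reference contrast is 15 dB, with power 0.94 at 66/33.

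**2. What happens to a patient withdrawn for a bleed before Day 8.**

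- The patient is in the FAS (SAP 4.1, 5.3).
- An audiogram is due at withdrawal (5.1.4, 4.5, with the Day 8 list in 4.2).
- SAP 5.3 does not mention that audiogram. Its rule for a missing Visit 5 is baseline carried forward, which gives a change of 0 dB.
- If the audiogram were instead filed as Visit 5 but fell outside Days 7 to 9, SAP 4.3 would flag it and leave the consequence to the blind data review.
- No later audiogram is requested (4.5), and Visits 6 and 7 are not imputed.

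**3. Size at Day 8.** The documents give no withdrawal rate and no recovery rate, so both are assumed. If k of n ancrod patients with a true mean gain of g are set to zero, the ancrod mean falls by k/n × g. I take k = 2. The 23 ancrod patients are an assumption: about 34 in total, split 23:11. The 66 are the planned number.

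| g (dB) | 2 of 23 | 2 of 66 |
|---|---|---|
| 10 | 0.87 | 0.30 |
| 20 | 1.74 | 0.61 |
| 30 | 2.61 | 0.91 |

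**4. The same effect as a rate, at 66/33.** Let f be the fraction of ancrod patients set to zero and m the placebo improvement. The contrast is (m + 15)(1 − f) − m. The ancrod variance is V = (1 − f) × 400 + f(1 − f)(m + 15)², SE = √(400/33 + V/66), and power = Φ(contrast/SE − 1.96). This simple two-group approximation leaves out the baseline and center terms.

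Example with m = 10 and f = 0.10: contrast = 25 × 0.9 − 10 = 12.5 dB; V = 360 + 56.25 = 416.25; SE = 4.29; power = Φ(0.95) = 0.83.

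| m (dB) | f = 5% | f = 10% | f = 20% |
|---|---|---|---|
| 0 | 14.3 dB, 0.92 | 13.5 dB, 0.89 | 12.0 dB, 0.82 |
| 10 | 13.8 dB, 0.90 | 12.5 dB, 0.83 | 10.0 dB, 0.64 |
| 15 | 13.5 dB, 0.88 | 12.0 dB, 0.79 | 9.0 dB, 0.54 |

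The last column exceeds the plan's whole 12% dropout allowance and is shown only as an outer bound.

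**5. Rescue, passages side by side.** Section 6.5 permits rescue if there is no improvement, or worsening, on Day 8. Section 6.4.1 exempts rescue from the on-study prohibition. Section 3.1 allows the switch on Day 8 and then describes Day 30 and Day 90 audiometry without leaving these patients out. SAP 4.2 defines a rescue-use subgroup. Against this, 5.1.4 and 9.3 name any exclusion criterion and carry no exemption, and a rescued patient meets criterion 11 and, on a systemic corticosteroid, criterion 27.

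**6. Day 30/90 if some rescued patients did leave.** This simulation assumes normal changes with SD 20 dB, a true contrast of 15 dB at both times, Day 8 to late correlation 0.8 and placebo improvement of 0, 10 or 15 dB. Patients with no gain at Day 8 leave with a stated probability, and the rest are analyzed as available.

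| Probability of leaving | Late contrast (dB) |
|---|---|
| 25% | 14.2 to 14.4 |
| 50% | 13.2 to 13.4 |
| 100% | 8.5 to 11.0 |

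At 100%, losses are 7% to 23% on ancrod and 23% to 50% on placebo.

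**The case against.** The case for leaving the text alone has several parts.

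- **The rule is optional, and an audiogram is taken.** It says patients may be withdrawn. Both points stand, so a reader who infers that Day 8 outcomes are certain to be lost goes beyond the documents. What remains is that sites may apply an optional rule differently, and that the SAP gives the withdrawal audiogram no role.
- **Drug interruption is already a separate step.** This is true: the paragraph on worsening health names bleeding. It does not say, as the fibrinogen rule does, that the remaining study activities continue.
- **Rescued patients are plainly meant to stay.** The exclusion list governs enrolment, and no passage directs withdrawal on rescue. A reader might infer from criteria 11 and 27 that non-improvers are to be withdrawn; 3.1, 6.4.1, 6.5 and SAP 4.2 point the other way. The conflict is one of wording. It barely touches the primary endpoint, because rescue starts at the Day 8 visit where that endpoint is measured.
- **The late effect could be made to look fatal.** If all improvers gained the same amount and every non-improver left, the late difference would be zero whatever the response rates. That result is built in by construction and is not a forecast.
- **Bleeding safety data are protected.** Mostly so: 9.1.13 follows serious and possibly related events after participation ends. What ends is the set of scheduled visits that would detect new events up to Day 90.
- **The FAS is not contradicted.** This is correct, since dropouts stay in it. The issue is whether they are measured.
- **Many criteria cannot be newly met through treatment.** This also stands, for example for screening fibrinogen.
- **Deleting the bullet would do little.** This stands as well. The investigator-discretion and adverse-event reasons would remain, so the remedy has to concern what is still measured after withdrawal.

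**Conclusion.** The point holds in a limited form. The withdrawal bullet reaches study participation, and at least one criterion, number 15, can be an effect of ancrod. Outcomes may therefore be lost in a treatment-related way, with a bled patient possibly scored as no change at Day 8 and missing at Days 30 and 90. With any positive true gain, this pulls the Day 8 comparison against ancrod.

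The size cannot be known from the documents. For two ancrod patients it is about 0.9 to 2.6 dB at the assumed 23, or 0.3 to 0.9 dB at the planned 66, against a 15 dB target. Those figures assume that the withdrawal audiogram is not used. The rescue limb is an inconsistency to be reconciled and mainly concerns Days 30 and 90. Overall this is a cheap improvement to make. It does not invalidate the primary analysis.

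**What to change.** 1. In Protocol 5.1.4 and 9.3, separate stopping study drug from leaving the study. State, as the Day 2 fibrinogen rule does, that patients who newly meet or are found to meet an exclusion criterion are still asked to attend the scheduled Day 8, 30 and 90 audiometry and adverse event assessments unless they decline.
2. Reconcile 5.1.4 and 9.3, read with criteria 11 and 27, with 3.1, 6.4.1 and 6.5, so that the text says one thing about participation after permitted rescue.
3. In SAP 5.3, state that an available post-baseline audiogram from withdrawal is used for Visit 5 before baseline is carried forward.

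Decisions on study drug and on clinical withdrawal stay with the sponsor and the investigator.

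The cost is a wording change to two matching lists, one sentence in the SAP and a few more visits that are already scheduled. The protocol change can help only patients who have not yet completed follow-up. The SAP sentence can cover every patient if it is added before unblinding.

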#### **5.1.5 Patient Log**

A patient screening log will be used to document the characteristics of all patients initially considered for inclusion into the study to ensure that the included sample does not differ significantly from the available patient population. The reason for exclusion should be given for all patients who are screened but not included.

For patients who are included, a separate patient log / identification list will be used to document name, birth date, gender and date of informed consent.

An example of the patient log/Identification list and the patient screening and enrolment log is provided in Appendix 17.1 and 17.2.

## **6 Study Drug and Related Procedures**

Each approved study site will receive the treatment kits from Nordmark Arzneimittel GmbH & Co. KG. The kits will be shipped refrigerated (+ 2 °C to + 8 °C).

|                                |                             |                      |
|--------------------------------|-----------------------------|----------------------|
| Protocol Amendment 7.1         | Study no.: NM-V-101         | Page 35 of 85 |
| Date of Amendment: 15 Feb 2018 | EudraCT No.: 2012-000066-37 |                      |

One treatment kit contains 2 cardboard boxes. One cardboard box contains 6 clear glass vials, the second cardboard box contains 3 clear glass vials. Each Vial contains an extractable volume of at least 1 ml

- solution for injection for s. c.-administration or
- concentrate for solution for infusion

corresponding to 70 IU / ml ancrod-fibrinogenase or placebo.

Upon arrival of the shipment at the study site:

- Inform Nordmark Arzneimittel GmbH & Co. KG immediately about the receipt of the treatment kits by fax or e-mail.
- Store the treatment kits immediately in a refrigerator according to the protocol. All treatment kits must be kept refrigerated until use and between all treatments at + 2 °C to + 8 °C but may not be frozen.
- Proceed with the thermometer and / or temperature logger according to the corresponding standard operating procedure document provided by Nordmark Arzneimittel GmbH & Co. KG.

In case of (potential) temperature excursions:

- the enclosed temperature logger should be read out immediately
- the potential impact on the quality of the study medication should be evaluated by Nordmark Arzneimittel GmbH & Co. KG.

All procedures to be fulfilled in case of potential temperature excursions by the clinical center, including e.g. temperature logger handling, are described in the corresponding standard operating procedure document provided by Nordmark Arzneimittel GmbH & Co. KG.

All used and unused vials of study medication must be maintained until the conclusion of the study. Diluted infusion solutions may be discarded after use. Unused vials should remain refrigerated (+ 2 °C to + 8 °C).

